### Procedures

Figure 1
describes the phases of the study. Participants from both groups will be randomly allocated to the groups. The study will be conducted over 4 to 5 weeks, followed by follow-up.

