### Preintervention, postintervention, and follow-up evaluation protocol

The pre- and post-intervention, as well as follow-up evaluation protocol has been prepared and is available with all the instruments used. The assessment procedures follow the European Physiotherapy Guideline for Parkinson's Disease.
39
The assessment will last 1 to 2 hours.

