The study groups should contain 15 patients each. The sample calculation considered how long each patient followed the protocol (∼ 2 months). We found no previous studies with the same outcomes and intervention protocol.

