### Statistical analysis

Initially, descriptive statistics should be used to analyze the data. To this end, summary measures must be calculated, followed by tables appropriate to the nature and measurement level of the variables involved.

The comparison of groups and moments in time throughout the intervention will be done after the verification with normality tests. If data were normally distributed, the repeat measures analysis of variance (ANOVA) will be used to compare groups (placebo and GVS) over time. If not normally distributed, we will use Freidmans's test for non-parametric data. Furthermore, the ANOVA test will be applied to assess the behavior of the quantitative variables before and after treatment and follow-up between groups, and repeated measures ANOVA will be implemented for effect within groups over consecutive treatment sessions. The significance level adopted for the statistical tests will be 5% (a = 0.05). Analyses and graphs will be done using the Statistical Package Social Sciences (SPSS Inc.) for Windows, version 10.0.

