### Ethical considerations

Before starting any research stage, participants will be fully informed verbally and in writing about all the stages of the research and its importance. They are free to accept or not to participate in the study. All participants must sign an informed consent form (ICF).

Participants will not be charged any fees or bonuses for participating and must be aware of their scientific contribution. The researchers will not disclose participants' data or the images captured on video. The data will be used exclusively for scientific purposes.

This research aims to promote new knowledge for professionals in this field. There will be direct benefits for patients, as they will be assessed and treated by an interdisciplinary team to reduce/remove body imbalance, gait alterations, and the risk of falls.

During the assessment and treatment, patients may experience dizziness, body imbalance, and difficulty walking. However, a researcher will always remain close to each patient to avoid falls and adapt the exercises according to their needs and threshold for dizziness and sensory-cognitive-motor difficulties. There will always be two examiners for the gait assessment.

The risks of GVS are related to its adverse effects: itching and discomfort at the stimulation site, as well as local burning. These can be minimized by thoroughly soaking the sponges to attach the silicone electrodes to the skin behind the ears in the mastoid area.

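### The repeated-measures ANOVA (or Friedman) comparison over three visits drops any patient who misses the 1-month visit, post-treatment score included; a mixed model would keep it

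*Protocol article*

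**What the plan says.** The Statistical analysis section names these methods:

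- For normally distributed data, "the repeat measures analysis of variance (ANOVA) will be used to compare groups (placebo and GVS) over time".
- Otherwise, "If not normally distributed, we will use Freidmans's test for non-parametric data".
- In addition, "the ANOVA test will be applied to assess the behavior of the quantitative variables before and after treatment and follow-up between groups". The rest of that sentence keeps repeated-measures ANOVA for within-group change across treatment sessions.

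The first sentence does not list its time points. They come from the section on the evaluation protocol ("The pre- and post-intervention, as well as follow-up evaluation protocol has been prepared") and from the third item above, which names the same three occasions. The Procedures section states "The study will be conducted over 4 to 5 weeks, followed by follow-up", and the aims at the end of the Introduction put follow-up at about one month.

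On size, the Sample size calculation section says "The study groups should contain 15 patients each". It gives no effect size, standard deviation, power or dropout allowance.

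**The concern.** Naming a test also settles who can be analysed by it. Classical repeated-measures ANOVA removes any case with an empty visit, and Friedman's test needs a complete block for each patient. Under either branch, a patient who finishes treatment, is scored on the Mini-BESTest afterwards and then misses the one-month visit contributes nothing to the group-by-time comparison. The lost data include the post-treatment score, which is a primary outcome and was properly observed.

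Two things are at stake. Precision falls in a trial of 30 patients, whatever the reason for the missed visit. And if the reason is related to arm or response, the patients compared are no longer the groups formed by randomisation, even at the post-treatment visit where nothing was missing.

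**Working it through.** **The plan's own figure.** The 15 per arm cannot be reproduced, because no inputs are given. Inverting n = 2(1.960 + 0.842)²/d² at n = 15, with two-sided alpha 0.05 and 80% power assumed, gives d = 2.802 × √(2/15) = 1.02 SD. With 12 per arm it becomes 2.802 × √(2/12) = 1.14 SD.

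**Assumptions.** All missed-visit rates, effect sizes and correlations below are assumed. Patients are taken to have pre and post scores and to miss only follow-up, with probability p.

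**Step 1: patients lost.** Complete cases per arm = 15(1 − p). The chance that an arm loses at least one observed post score is 1 − (1 − p)^15. The standard error of an unadjusted difference grows by √(1/(1 − p)).

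| p | Complete per arm | Chance of at least one loss | Standard error factor |
|---|---|---|---|
| 10% | 13.5 | 0.79 | 1.05 |
| 20% | 12.0 | 0.96 | 1.12 |
| 30% | 10.5 | above 0.99 | 1.20 |

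Keeping every observed post score leaves 15 per arm for the post contrast in all three rows.

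**Step 2: power when the loss is random.** This was simulated with 4,000 runs per setting, three visits, correlation 0.6 between visits and a true effect of 0.8 SD. The baseline-adjusted post difference was estimated from all post scores and then from complete cases only. It isolates the effect of deletion and is not itself the repeated-measures ANOVA.

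| p | Power, all post scores | Power, complete cases |
|---|---|---|
| 10% | 0.75 | 0.69 |
| 20% | 0.75 | 0.62 |
| 30% | 0.74 | 0.54 |

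The estimate stayed at about 0.80 SD throughout: precision is lost and no bias arises.

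**Step 3: a case with upward bias.** Take no true effect and post-treatment change standardised to SD 1. In the GVS arm, the k patients lowest on a score correlated r with change miss follow-up. The expected values of the four smallest of 15 standard normals are −1.736, −1.248, −0.948 and −0.715. The arm mean after deletion shifts by r × (sum of the k absolute values)/(15 − k).

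- k = 2, r = 0.5: 0.5 × 2.984/13 = 0.115 SD
- k = 3, r = 0.5: 0.5 × 3.932/12 = 0.164 SD
- k = 4, r = 0.5: 0.5 × 4.647/11 = 0.211 SD
- k = 3, r = 1: 3.932/12 = 0.328 SD

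If the lowest-scoring placebo patient is also lost, that arm shifts by r × 1.736/14 = 0.124r. The k = 3 difference falls to 0.102 SD at r = 0.5 and to 0.204 SD at r = 1.

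**Step 4: a case with downward bias.** In the setting of Step 2, GVS patients miss follow-up at random, while in the placebo arm only patients with below-median post scores miss it, at the same overall rate. The true 0.80 SD is then estimated from complete cases as 0.74, 0.67 and 0.58 SD at 10%, 20% and 30%. Using all post scores it stays at 0.80.

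Steps 3 and 4 point in opposite directions under equally hypothetical dropout patterns.

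**The case against.** **The separate ANOVA.** The strongest objection is that the plan names a plain between-group ANOVA alongside the repeated-measures one. Because the same sentence uses repeated-measures ANOVA for something else, the plain version may well be meant visit by visit. It would then keep the post score of a patient who misses follow-up. This stands in part. A reader might infer that the score is lost from every analysis in the plan, and the text does not support that. But neither does it say that the ANOVA is run per visit, or that it carries the post-treatment conclusion. The group-over-time comparison remains complete-case either way.

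**Direction of bias.** A reader might also infer that deletion would favour GVS. The documents do not settle this. Itching, discomfort and local burning are tied to GVS, but the section also says they can be reduced, and nothing says that they lead to withdrawal. The statement "During the assessment and treatment, patients may experience dizziness, body imbalance, and difficulty walking" is not specific to an arm. No dropout rate is given for either group.

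**Missing-data policy.** Analysis sets, imputation and continued assessment after stopping treatment may be set out in a full protocol or analysis plan that is not shown. That is fair: the article adopts no completers-only rule, and its silence on whether early stoppers are still assessed is no fault of the article. An unseen plan could also impute before the ANOVA. What remains is a property of the named methods, which on their own cannot use a partly observed patient.

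**Conclusion.** The point holds for the group-by-time comparison. As named, both the repeated-measures ANOVA and the Friedman fallback discard observed post-treatment scores whenever follow-up is missed, and an available method does not. The mechanism follows from the tests and the visit schedule.

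The size depends on assumed rates. At 10% to 30% missed follow-up, complete cases average 13.5 down to 10.5 per arm, and simulated power for 0.8 SD falls from about 0.75 to between 0.69 and 0.54. Bias needs missingness related to arm or response, and its sign is open: about +0.16 SD in one illustrative case, and an attenuation of 0.06 to 0.22 SD in another (0.80 less 0.74, 0.67 or 0.58). If everyone attends every visit, there is no loss. The change should be made, but nothing here shows that the trial's result would be biased.

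**What to change.** Replace the repeated-measures ANOVA/Friedman group comparison with a linear mixed model containing arm, visit and arm-by-visit. Include all randomised patients in their allocated arm with every observed score, and read the post-intervention and follow-up contrasts from that model. Check normality on its residuals instead of using a test to switch to Friedman.

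The cost is a wording change in the Statistical analysis section and a mixed-model routine; check that the named SPSS version 10.0 provides one. No visits or patients are added. The model's validity rests on missingness being at random given the observed scores. That is weaker than what a complete-case comparison needs, but it is still an assumption and should be stated.

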**Methods:**

A randomized, placebo-controlled clinical trial. Participants with PD, diagnosed through the Hoehn & Yahr scale (HY) 2 or 3, will be allocated to groups. Pre- and postintervention and follow-up assessments will follow a structured protocol of physical-functional instruments, as recommended in the European Guidelines for managing people with PD. The intervention for both groups will follow the American Neurofunctional Physical Therapy Guideline for managing people with PD.

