In this context, our principal aim was to analyze the effects of GVS associated with physical-functional exercise on the motor control of PD patients. Our specific objectives were to analyze the effects of this treatment on body balance, gait, postural transfer, manual dexterity, physical capacity, confidence in body balance, risk of falling, and quality of life in patients with PD. Furthermore, we aim to analyze its effects on the safety and satisfaction of patients after treatment, as well as its permanent effects over 1 month.

Our hypotheses are that people with PD undergoing treatment with GVS associated with physical-functional exercise will show better motor control performance than those without GVS (placebo). Furthermore, they will perform better in body balance, gait, postural transfer, manual dexterity, and physical capacity tasks. We also expect an improvement in their quality of life, when compared with the placebo group. We believe GVS associated with physical-functional exercise is safe and satisfactory for PD patients, and that its effects will last approximately 1 month after treatment, with patients maintaining physical-functional exercise.

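### The 1-month hypothesis has no designated test, and the group-by-time term of the named repeated-measures ANOVA cannot tell a lasting GVS effect from one that has gone

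*Protocol article*

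**What the plan says.** The last paragraphs of the Introduction make persistence an aim, "as well as its permanent effects over 1 month", and a hypothesis: "its effects will last approximately 1 month after treatment, with patients maintaining physical-functional exercise". The Abstract (Methods) sets three assessment occasions: "Pre- and postintervention and follow-up assessments will follow a structured protocol of physical-functional instruments".

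The Statistical analysis section describes three analyses for normally distributed data:

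- For the arms over time: "the repeat measures analysis of variance (ANOVA) will be used to compare groups (placebo and GVS) over time".
- A further between-arm analysis: "the ANOVA test will be applied to assess the behavior of the quantitative variables before and after treatment and follow-up between groups".
- A within-arm analysis: "repeated measures ANOVA will be implemented for effect within groups over consecutive treatment sessions".

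The section does not say which term of the first analysis is read, whether the second is run visit by visit or pooled, or which of them tests the 1-month hypothesis. The sample size section gives 15 patients per group.

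**The concern.** With two arms and three visits, the usual between-arm reading of a repeated-measures ANOVA is the group-by-time term. This is an omnibus test on 2 degrees of freedom. It asks whether the arms differ in their pattern over the three visits, so a benefit seen only straight after treatment is enough to make it significant.

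Persistence is a narrower question: does GVS differ from placebo at the 1-month visit? If the omnibus term were taken as the answer, a significant result would carry no information on whether anything remains at 1 month. At stake is a stated hypothesis with direct practical meaning for a ten-session treatment, although the article does not single it out as the primary outcome.

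**Working it through.** **Inputs from the article.** Two arms of 15; three visits (pre, post, follow-up); 5% significance level. The follow-up visit is taken to be the one at about 1 month named in the aims. The 15 per arm cannot be reproduced, because no effect size, SD or power is given; it is used here only as an input.

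**Assumptions (not in the article).** Normal scores with SD 1 at each visit, no true baseline difference, and a GVS effect d at post, with 0.8 SD as the main case. Three states at follow-up: sustained (0.8), half lost (0.4), gone (0).

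**Step 1. Group-by-time term, equal correlations ρ.** The power depends on the centred sum of squares of the arm differences over the three visits.

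- Sustained (0, d, d): mean 2d/3; squares 4d²/9 + d²/9 + d²/9 = 2d²/3.
- Gone (0, d, 0): mean d/3; squares d²/9 + 4d²/9 + d²/9 = 2d²/3.

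The noncentrality is λ = (n/2) × (2d²/3) / (1 − ρ), on 2 and 56 df, and is the same in both cases whatever d and ρ are.

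- d = 0.8, ρ = 0.5: λ = 7.5 × 0.4267 / 0.5 = 6.4; power 58.9% in both cases.
- d = 0.5, ρ = 0.5: λ = 2.5; 26.1% in both.
- d = 1.0, ρ = 0.5: λ = 10; 79.3% in both.
- d = 0.8, ρ = 0.7: λ = 10.67; 82.0% in both.

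**Step 2. Group-by-time term, unequal correlations.** Simulated with the Greenhouse-Geisser correction, d = 0.8. The equality no longer holds exactly, and the vanished effect is now significant more often. With an autoregressive correlation of 0.7 the rates are 67% sustained and 75% gone. The table gives two further patterns.

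**Step 3. Group main effect** (correlations 0.6 with baseline, 0.8 post to follow-up). The variance of a patient's three-visit mean is (3 + 2 × (0.6 + 0.6 + 0.8)) / 9 = 0.778, so the standard error of the arm difference is √(0.778 × 2/15) = 0.322. Sustained: (1.6/3) / 0.322 = 1.66, which gives 36% on 28 df (38% in one simulation run). Gone: (0.8/3) / 0.322 = 0.83, which gives 13%.

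**Step 4. Unadjusted comparison of arms at follow-up.** 0.8 / √(2/15) = 2.19, which gives 56% on 28 df. For 0.4 SD: 1.10, 18%. For no effect: 5%.

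**Step 5. Comparison at follow-up adjusted for the pre-treatment score.** The residual variance is 1 − 0.6² = 0.64, so the standard error is about √(0.64 × 2/15) = 0.292 and the ratio 0.8 / 0.292 = 2.74. Simulation, which allows for chance baseline imbalance, gives about 74%; 25% if half is lost; 5% if gone.

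| Test (15 per arm, 0.8 SD at post) | Sustained | Half lost | Gone |
|---|---|---|---|
| Group-by-time, correlations 0.6/0.8 | about 70% | 57–60% | 76–78% |
| Group-by-time, correlations 0.5/0.9 | about 58% | 46–48% | about 70% |
| Group main effect, 0.6/0.8 | 36–38% | – | about 13% |
| Arms at follow-up, unadjusted | 56% | 18% | 5% |
| Arms at follow-up, baseline-adjusted, 0.6/0.8 | about 74% | about 25% | 5% |

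Ranges are the spread between simulation runs or between simulation and exact calculation.

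**The case against.** The strongest reply is that the section already contains a between-arm ANOVA that covers follow-up. The same sentence sets it apart from the repeated-measures ANOVA, so a per-visit reading is natural. With two arms that is a 1-df comparison at follow-up, and it does separate the cases (56% against 5%). This stands in part. A reader might infer that the plan cannot answer the 1-month hypothesis at all, and the document does not support that. What remains is that the sentence can also be read as a second pooled test, is not linked to the hypothesis, and uses no baseline adjustment.

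It can also be said that contrasts following an ANOVA are often left to an analysis plan, which is not shown. That is fair for detail. But the article does choose its tests, and a better-aimed and more powerful analysis of data already being collected is a matter of method, not only of missing text.

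Other strong readings go too far:

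- *That the omnibus analysis is always just as often significant for a vanished effect.* This is exact only for the group-by-time term with equal correlations. The article does not say which term is read, and the group main effect is significant much less often when the effect has gone. That term still averages in the pre and post visits, so it does not isolate 1 month either.
- *That the plan would infer persistence from a non-significant change between post and follow-up within the GVS arm.* The within-arm ANOVA is stated for consecutive treatment sessions; no such post-to-follow-up test is named.
- *That the persistence claim has no error control, or that a significant interaction will be reported as a lasting effect.* The section sets 5% for its tests, and no sentence announces that interpretation.

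**Conclusion.** The concern holds in limited form. The article states a 1-month hypothesis but does not say which test decides it, and the group-by-time term of the named repeated-measures ANOVA cannot. That term has identical power for a sustained and a vanished effect under equal correlations, a result that does not depend on the effect size or the correlation. Under the assumed 0.6/0.8 correlations it is about 70% against 76% to 78%. The group main effect does not isolate the 1-month visit. The further between-group ANOVA may do so, but the text leaves this open. The percentages other than the equality rest on the assumed 0.8 SD effect, normal scores and correlations.

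The aim's wording is a small related matter. One follow-up visit can show an effect present at that visit; it cannot show a permanent one. The article probably means no more than that, and should say so.

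**What to change.** In the Statistical analysis section, name the GVS-minus-placebo difference at the 1-month visit, adjusted for the pre-treatment score and reported with its 95% CI, as the test of the 1-month hypothesis. Say whether the further between-group ANOVA is meant to be this comparison; if so, replace it with the adjusted form. Add that a significant group-by-time term alone is not evidence of persistence. In the Introduction, reword the aim and hypothesis as *effect still present at the 1-month visit*.

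The cost is a few sentences and no new data. Under the assumptions above, the adjustment raises power at 1 month from 56% to about 74%. The downside for the investigators is that a persistence claim becomes harder to make, since it must rest on a difference at 1 month and not on a difference at any visit.

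### The non-normal branch replaces the two-group ANOVA with Friedman's test, which has no group term, so that branch names no valid test of GVS against placebo

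*Protocol article*

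**What the plan says.** The trial's question is between groups. The Introduction expects that patients given GVS plus exercise "will show better motor control performance than those without GVS (placebo".

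The Statistical analysis section sets out the route in this order:

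- **Normality check first:** "The comparison of groups and moments in time throughout the intervention will be done after the verification with normality tests".
- **Normal data:** "the repeat measures analysis of variance (ANOVA) will be used to compare groups (placebo and GVS) over time".
- **Non-normal data:** "If not normally distributed, we will use Freidmans's test for non-parametric data".
- **A further sentence, with no normality condition:** "the ANOVA test will be applied to assess the behavior of the quantitative variables before and after treatment and follow-up between groups". It also adds a within-group repeated-measures ANOVA over the treatment sessions.
- **Level:** "The significance level adopted for the statistical tests will be 5% (a = 0.05").

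No between-group rank test is named anywhere. Under Sample size calculation, "The study groups should contain 15 patients each". Patients are assessed before the intervention, after it and at follow-up, and both groups receive the exercise programme.

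**The concern.** Friedman's test is written in as the substitute for the analysis that compares the two arms, but it answers a different question: whether patients' scores differ between visits. It can be run on all 30 patients together or separately in each arm, and neither version compares the arms.

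This matters here because exercise is given to everyone. Change over time is expected in both arms even if GVS does nothing. A significant Friedman result in the pooled data could come entirely from exercise. If the test is run arm by arm, one p-value below 0.05 and one above it can arise by chance between two arms that behave identically. Any outcome that fails the normality check meets this problem, including the two primary instruments, the Mini-BESTest and the ABC Scale.

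**Working it through.** **Step 1. Does the statistic contain the arm?** With n patients, k visits and R_j the sum of the within-patient ranks at visit j, Friedman's statistic without ties is

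Q = 12 / [n k (k + 1)] × Σ R_j² − 3 n (k + 1), on k − 1 degrees of freedom.

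Pooling both arms gives n = 2 × 15 = 30, and k = 3. Then 12 / (30 × 3 × 4) = 1/30 and 3 × 30 × 4 = 360, so Q = Σ R_j² / 30 − 360 on 2 degrees of freedom. No term refers to arm. As a check, arm labels were permuted in 200 simulated data sets per scenario, and the pooled p-value never changed. It carries no information on GVS against placebo. This step needs no assumption about the data.

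**Step 2. How often would it be significant with no GVS effect?** The protocol gives no between-visit correlation and no expected exercise effect, so both are assumed and shown as a range. The set-up is 15 patients per arm, 3 visits, normal data, the same improvement in both arms at both later visits, and two-sided 0.05.

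| Correlation | Shared improvement (SD) | Pooled Friedman p < 0.05 |
|---|---|---|
| 0.3 | 0.2 | about 12% |
| 0.5 | 0.3 | about 30% |
| 0.5 | 0.5 | about 66% |
| 0.7 | 0.5 | about 88% |
| 0.8 | 0.8 | about 100% |

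Run separately in each arm, the pattern 'GVS arm significant, placebo arm not' occurred in about 1% to 24% of trials. It was most frequent at correlation 0.7 and 0.5 SD. It was rare at correlation 0.8 and 0.8 SD, where both arms nearly always reject. A Mann-Whitney test on change from baseline rejected in 4% to 5% of trials, as it should.

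**Step 3. Does the result depend on normal data?** The simulation was repeated with skewed errors: patient SD 0.7 and centred exponential error SD 0.7, so each measurement has SD √(0.49 + 0.49) = 0.99 and the correlation is 0.49/0.98 = 0.5.

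| Shared improvement | Pooled Friedman | 'GVS significant, placebo not' | Between-group tests on change |
|---|---|---|---|
| 0.5 | 89% | 24% | 4.9% (both tests) |
| 0.8 | 99% | 11% | 4.1% (Mann-Whitney), 4.7% (t-test) |

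With a real GVS effect of 0.8 or 1.0 in these units and no shared improvement, Mann-Whitney on change had about 65% and 83% power. A rank test that does answer the question is therefore available.

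**Step 4. How often would an outcome enter this branch?** The protocol does not say which normality test is used, on what data, or how many times.

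- One test per outcome at 5%: about 5% of truly normal outcomes fail.
- Six tests (2 arms × 3 visits), with any one failing: 1 − 0.95⁶ = 26.5% if independent. The simulated figure was 26.1%.
- Six tests with the skewed errors of Step 3: about 53% to 56%.

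**Step 5. What does the additional ANOVA do?** The sentence that adds it follows the Friedman sentence and carries no condition. Two readings are open.

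- *It always applies.* The arms are compared even when the normality check fails, but by the parametric method that the check exists to rule out. Friedman and ANOVA results would then stand side by side for one outcome, with no rule on which decides.
- *It belongs to the normal branch.* Then no between-group test remains for an outcome that fails the check.

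The text does not settle which is meant.

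**The case against.** The strongest reply is that the plan does keep a between-group comparison. A reader might infer from the Friedman sentence alone that GVS against placebo is not tested at all once normality fails. The document does not establish that: the next sentence names an ANOVA between groups without a normality condition, and read literally it survives. This objection stands against the stronger reading. It does not make Friedman's test a valid substitute, and it leaves the section contradicting its own normality check.

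A second reply is that the simulated rates depend on chosen inputs. That is right, and it is why a range is given. The 88% figure describes one assumed scenario towards the upper end. Arm-by-arm disagreement in either direction was about twice the rate quoted above, but only the half that favours GVS would mislead in its favour. The 26% failure rate for the normality check likewise assumes six tests, which the protocol does not specify. The argument in Step 1 depends on none of these figures.

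A third reply is that nobody would report a time effect as a treatment effect, given that the hypothesis is stated between groups. How the result would be reported cannot be known from the document. The point is only that the named test cannot support the stated hypothesis.

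Finally, a separate analysis plan may exist. That would excuse missing detail, but here the article names a specific test for a specific purpose, and the test does not serve it.

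**Conclusion.** Wrong as written. In the non-normal branch the named test cannot compare the arms. The only between-group analysis left is an ANOVA whose relation to the normality check is undefined. This follows from the form of Friedman's test and the wording of the section, without any assumption.

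The size does rest on assumptions. With no GVS effect, a shared exercise improvement makes pooled Friedman significant in about 12% to 100% of trials over the correlations (0.3 to 0.8) and improvements (0.2 to 0.8 SD) considered. The misleading arm-by-arm pattern in favour of GVS appears in about 1% to 24%. By chance alone, about 5% of truly normal outcomes would enter this branch with one normality test, and about 26% with six.

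That the trial's question goes entirely untested holds only if the additional ANOVA is confined to the normal branch, which the document does not say.

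**What to change.** 1. Remove Friedman's test as the group comparison, and do not let a normality pre-test choose the primary analysis.
2. For each primary outcome, prespecify one between-group analysis: a linear model of the post-intervention score on arm and baseline score. Use the same model at the 1-month follow-up for the persistence objective.
3. Name one distribution-free sensitivity check: a permutation test of the same adjusted arm difference.
4. State that this model replaces the additional between-group ANOVA, and that within-group analyses over time are descriptive and not evidence of a GVS effect.

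If the sponsor prefers a minimal repair to steps 1 to 3, a Mann-Whitney test on change from baseline in place of Friedman's test would correct the wrong test. The role of the additional ANOVA would still have to be stated.

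The cost is a few sentences in the Statistical analysis section, with no new data and no extra patients. It should be done before outcome data are seen, because afterwards the choice of test would be open to influence from the results.

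### The within-group ANOVA over consecutive sessions has no matching assessment in the published text, and the plan does not say that only the between-arm comparison supports conclusions about GVS

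*Protocol article*

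**What the plan says.** All of the following is in the protocol article.

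- **Analyses named (Statistical analysis).** For normally distributed data, "the repeat measures analysis of variance (ANOVA) will be used to compare groups (placebo and GVS) over time". Otherwise, "If not normally distributed, we will use Freidmans's test for non-parametric data". A further sentence adds two more. The one within each arm reads "repeated measures ANOVA will be implemented for effect within groups over consecutive treatment sessions". The one that sets the arms against each other reads "the ANOVA test will be applied to assess the behavior of the quantitative variables before and after treatment and follow-up between groups". One significance level of 5% covers all of them.
- **Assessments described.** The Abstract and the evaluation section name the same three occasions: "The pre- and post-intervention, as well as follow-up evaluation protocol has been prepared and is available with all the instruments used". One assessment takes 1 to 2 hours.
- **Treatment (Intervention; Abstract, Methods).** There are ten sessions, and both groups follow the same guideline-based exercise programme.
- **Hypotheses (Introduction).** Patients given GVS with exercise are expected to do better than those given exercise with placebo, and the authors expect "that its effects will last approximately 1 month after treatment".
- **Size (Sample size calculation).** "The study groups should contain 15 patients each".

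**The concern.** Two things do not fit together.

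First, an analysis over consecutive sessions needs an outcome recorded at sessions, and the text describes none. The safety and satisfaction questionnaire is described as recording events and satisfaction after treatment, not session by session.

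Second, if the three scheduled visits are used instead, the within-group test answers a different question from the hypothesis. A significant change in the GVS arm mixes any GVS effect with exercise, retesting and placebo response, and the placebo arm has those too. A non-significant change from post-treatment to follow-up in 15 patients would say little about whether a gain had lasted.

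The between-group analyses would answer the question, but the section does not give them priority. On the non-normal branch the test named is Friedman's, which tests change within subjects and does not compare two independent arms. It is not stated whether the ANOVAs in the further sentence would still be run on that branch. A within-arm result could then be the most prominent p-value available.

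**Working it through.** **1. Analysis against schedule.** The analysis's time factor is treatment sessions, of which there are ten. The assessment occasions described are three: pre, post and follow-up. A battery of 1 to 2 hours is unlikely to be repeated at each session without being mentioned. Figure 1 and the full evaluation protocol are not shown, so the finding is that the text describes no session-level outcome, not that none exists.

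**2. How often within-arm tests would mislead.** The plan gives no effect size, SD or correlation, so there is no figure of its own to reproduce.

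From the document: n = 15 per arm, alpha = 0.05, three visits. Assumed: no GVS effect; the same true gain g (in SD) in both arms, present at post-treatment and kept at follow-up; equal correlation r between visits.

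For a one-arm repeated-measures ANOVA with visit means 0, g, g:

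- sum of squared deviations of the means = 2g²/3
- noncentrality = 15 × (2g²/3) / (1 − r)
- power p = P(noncentral F with 2 and 28 df > 3.340)
- P(only the GVS arm significant) = p(1 − p), because the arms are independent; this cannot exceed 0.25

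Example, g = 0.4 and r = 0.7: 2 × 0.16 / 3 = 0.1067; 15 × 0.1067 / 0.3 = 5.33; p = 0.486; 0.486 × 0.514 = 0.250.

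P(only the GVS arm significant), with no GVS effect:

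| Shared gain | r = 0.5 | r = 0.6 | r = 0.7 | r = 0.8 |
|---|---|---|---|---|
| 0.2 SD | 9.7% | 10.9% | 12.8% | 16.4% |
| 0.3 SD | 15.4% | 17.6% | 20.7% | 24.4% |
| 0.4 SD | 21.4% | 23.5% | 25.0% | 22.2% |
| 0.5 SD | 24.8% | 24.7% | 21.5% | 12.1% |
| 0.6 SD | 23.6% | 20.1% | 13.2% | 4.0% |
| 0.8 SD | 11.5% | 6.2% | 1.9% | 0.1% |

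Simulation of 20,000 trials per scenario agrees: at r = 0.6, gains of 0.2, 0.3, 0.4, 0.5, 0.6 and 0.8 SD gave 11%, 18%, 24%, 25%, 20% and 6%. With ten session time points and a gradual gain, r = 0.6, the figures were 9%, 15%, 22%, 25%, 21% and 5%, so session-level data would not remove the problem.

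**3. The between-arm test on the same data.** The group-by-time F-test rejected in 4.8% to 5.2% of simulated trials in every scenario, as it should at 5%.

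**4. The Friedman branch.** At r = 0.6 and gains of 0.2 to 0.5 SD, Friedman tests run in each arm were significant in exactly one arm in 18% to 48% of trials. By symmetry half of these, about 9% to 24%, are GVS only.

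**5. Persistence.** Suppose a gain of 0.4 SD is wholly lost by follow-up. The paired difference has SD √(2(1 − r)), so at r = 0.7 the standardized change is 0.4 / √0.6 = 0.516. A paired t-test in 15 patients is then non-significant in 54% of trials (70% at r = 0.5, 38% at r = 0.8). Non-significance is weak evidence that an effect lasts.

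**The case against.** The strongest reply is that the between-arm comparison is already planned, twice, and that one of those analyses covers both post-treatment and follow-up. The within-group test is an addition, and describing each arm's course is common practice. This stands, and it limits the point.

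Three stronger readings are tempting, and the document supports none of them:

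- A reader might infer that GVS will be declared effective if its arm is significant and placebo is not. No section says so, and the hypothesis is worded between groups.
- A reader might infer that a non-significant change from post-treatment to follow-up will be taken as persistence. The Introduction states an expectation about duration, not a rule for judging it.
- A reader might infer that nothing is measured at sessions. The article is condensed, and Figure 1 and the full evaluation protocol are not shown.

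It is also fair to say that the 25% figure is the mathematical ceiling, reached only when each within-arm test has power near one half. With a large shared gain both arms are nearly always significant, and the misleading pattern becomes rare.

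Finally, naming a session-level variable and its timing would cure the mismatch as well as deletion would. It would not turn a within-arm test into evidence about GVS, as the ten-time-point simulation shows.

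What remains is that the section gives the between-arm comparison no priority over the within-arm one, and that for non-normal data it names a test that does not compare the arms.

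**Conclusion.** The concern holds in limited form. In the text shown, the session-level within-group ANOVA has no matching assessment. Run on the three visits, it cannot separate GVS from what both arms share. Misattribution is a risk in how results may be read, because no analysis is designated for the efficacy or persistence conclusion.

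For small-to-moderate shared gains (0.2 to 0.5 SD, correlation 0.5 to 0.8) the risk is about 10% to 25% of trials with no GVS effect. At 0.8 SD it is between about 11.5% and 0.1%, depending on the correlation. These sizes rest on assumed gains and correlations, an equal true change in both arms, and equal correlation between visits. Severity: should-fix, since valid between-arm analyses are already named.

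**What to change.** In the Statistical analysis section:

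1. Remove the within-group ANOVA over consecutive sessions.
2. State that conclusions about GVS rest only on the baseline-adjusted between-arm difference, with 95% CI: at post-intervention for efficacy and at 1 month for persistence.
3. Have this apply to non-normal data too, so that Friedman's test does not stand in for the comparison of arms.
4. Report change within each arm descriptively, without p-values.

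The cost is analysis wording only. The baseline, post-treatment and follow-up data are already planned, no patient or visit is added, and there are fewer tests to run.
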